### Study population

The cohort will include all adult (aged 16 years and over) HCWs captured by HR records or registered with at least one professional regulator on 1 February 2020, excluding those which linkage to EHRs is unsuccessful. HCWs with missing ethnicity, occupation, age, sex or postcode will be excluded from the main analysis. For the HR substudy, only those actively working will be included, thus excluding those on parental, sickness or disability leave for the duration of study period.

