### Observation period

Follow-up commences on the index date (1 February 2020) (or date of return/commencement of employment for the HR substudy) and continue until either their death date (COVID-19 related or due to other causes) or the study end date (31 January 2021). For the HR substudy, those leaving NHS employment during the study period will be included up until this date, at which point they will be censored.

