### Outcomes

The main outcomes are COVID-19 diagnosis (confirmed and suspected, confirmed only), hospitalisation (all, COVID-19 specific, ITU admission) and mortality (all-cause, COVID-19 specific). The definitions, data sources and a summary of planned analyses for these outcomes are provided in table 3: COVID-19 outcomes and definitions, identified via listed data sources, to be assessed in UK HCW cohort and within listed subgroups, via listed analysis approach in the planned study.

**Table 3 T3:** COVID-19 outcomes and definitions, identified via listed data sources, to be assessed in UK healthcare worker cohort and within listed subgroups, via listed analysis approach in the planned study

Outcomes		Definitions	Data sources	Subgroups	Analysis approach (output)
COVID-19 diagnosis	Confirmed COVID-19 diagnosis	A positive swab test for SARS-CoV-2 during the study period	PHE Pillar 1 (PHE laboratories or NHS hospital) and Pillar 2 (wider population) testing data^1^		Poisson regression (IRR)
	Suspected COVID-19 diagnosis	Self-reporting of either a positive SARS-CoV-2 test or combination of symptoms shown to be predictive of positive testing^2^ during the study period or suspected case SNOMED CT codes (NHS Digital) recorded during the study period	COVID-19 Symptom Study app and primary care data		Poisson regression (IRR)
Hospitalisation	All hospitalisations	Any hospital admission recorded during the study period	Secondary care and CHESS data	Confirmed COVID-19 diagnosis	Logistic regression (OR)
	COVID-19 hospitalisations	hospital admissions with COVID-19-specific ICD-10 codes^3^ during the study period or positive swab test for SARS-CoV-2 recorded during or within 28 days prior to admission	Secondary care, CHESS, PHE Pillar 1 (PHE labs or NHS hospital) and Pillar 2 (wider population) testing data^1^	Confirmed COVID-19 diagnosis	Logistic regression (OR)
	COVID-19 ITU admissions	Admissions to ITU during the study period	Secondary care, CHESS, and intensive care audit data	Confirmed COVID-19 diagnosis	Logistic regression (OR)
Mortality	All-cause mortality	Any death registration recorded during the study period	ONS mortality, primary care and secondary care data	Confirmed COVID-19 diagnosis COVID-19 hospitalisations COVID-19 ITU admissions	Flexible parametric time-to-event regression (HR)

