### Outcome incidence

Adjusted annual and quarterly incidence rates, per 100 000 HCWs, for each outcome will be calculated for each country where available. Meta-analysis methods will combine the country-specific estimates to give an overall UK incidence rate estimate. Adjusted incidence rates by ethnicity and occupation will be calculated in the same way. All incidence rates will be adjusted for the four core predictors (age, sex, comorbidities and deprivation) using standardisation methods. The incidence rates of each outcome will be reported as the rate of cases in the final UK HCW cohort and within subgroups who have experienced preceding COVID-19 events (table 3: COVID-19 outcomes and definitions, identified via listed data sources, to be assessed in UK HCW cohort and within listed subgroups, via listed analysis approach in the planned study). The time between diagnosis and outcomes will be summarised and cumulative incidence curves will be plotted.

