## Discussion and limitations

As COVID-19 spreads, the number of cases requiring medical intervention will continue. It is crucial to maintain the healthcare system in the UK and control secondary transmission of COVID-19, and measures to identify and protect the HCWs most vulnerable to infection and adverse outcomes must be implemented. However, current COVID-19 risks in HCWs, particularly within those from historically disadvantaged populations, are poorly understood.

Published evidence of COVID-19 outcomes in HCWs are generally from small studies, in single centre or region settings outside the UK, which have not investigated associations with ethnicity.^30^ COVID-19 studies which use observational data from non-random sampling, such as hospital admissions or voluntary participation, may be affected by collider bias.^31^ One such study assesses outcomes using voluntary self-reported data from symptom trackers only,^32^ thus results are at risk of selection bias due to reliance on accurate self-reporting of exposures and outcomes. A recent study assessing risks of hospitalisation in HCWs and household members in Scotland^18^ had insufficient numbers of HCWs from ethnic minority groups to reliably estimate associations between COVID-19 outcomes and ethnicity. This planned study is, to the authors’ knowledge, the first UK-wide study to assess the relationship between ethnicity and COVID-19 outcomes in HCWs. This large study incorporates ambitious linkage of multiple anonymised HR, professional registration and NHS data sets providing UK-wide coverage of clinical and non-clinical HCWs. However, the lack of a single UK-wide database capturing all HCWs actively working limits our ability to identify all HCWs across all regions. We aim to identify non-clinical ancillary staff not directly employed by the NHS by incorporating contracting organisations.

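### Suspected COVID-19 diagnosis counts app self-reports as cases but keeps all healthcare workers in the denominator, so its rate ratio partly measures app uptake if uptake differs by ethnic or occupational group.

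*Protocol article*

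**What the plan says.** The Outcomes section of the protocol article lists the first main outcome as "COVID-19 diagnosis (confirmed and suspected, confirmed only". Table 3 has one row for confirmed and one for suspected diagnosis. The suspected row can be met in two ways:

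- "Self-reporting of either a positive SARS-CoV-2 test or combination of symptoms shown to be predictive of positive testing"; or
- "suspected case SNOMED CT codes (NHS Digital) recorded during the study period".

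Its data sources are "COVID-19 Symptom Study app and primary care data". Its subgroup cell is blank and its analysis is Poisson regression giving an incidence rate ratio (IRR).

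Other sections fix the denominator and the model:

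- **Study population:** all adult healthcare workers (HCWs) in HR or regulator records, "excluding those which linkage to EHRs is unsuccessful". App use plays no part in entry.
- **Observation period:** "Follow-up commences on the index date (1 February 2020"; follow-up runs to death or 31 January 2021. In the HR substudy it starts later for those returning or joining, and leavers are censored. App enrolment does not affect it.
- **Outcome incidence:** "The incidence rates of each outcome will be reported as the rate of cases in the final UK HCW cohort", and also within subgroups with a preceding COVID-19 event. App users are not one of those subgroups.
- **Associations between ethnicity, occupation and COVID-19 outcomes:** the models contain ethnicity, occupation, their interactions, age, sex, comorbidities and deprivation.
- **Sensitivity and additional analyses:** no listed analysis drops app-derived cases or restricts to app users.

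**The concern.** A person without the app cannot become a case by the app route, but still contributes up to a full year of person-time as a non-case. An app user's time before enrolment is also counted. The observed rate in a group is therefore the rate of coded illness plus a part that scales with the share of that group using the app.

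Ethnicity is the main exposure, and occupation is also of primary interest. If either is related to app use after adjustment for the four core predictors, the rate ratio differs from 1 even when illness rates are equal, and a real difference can be shrunk, hidden or inflated. A large cohort does not help: it narrows the interval around the wrong value.

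The limitations stated for suspected cases do not cover this. The Discussion concedes under-diagnosis, possible collider bias where testing is restricted, and false positives. Case capture that varies between the groups being compared is a separate problem.

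**Working it through.** The plan states no figure for suspected diagnosis, so there is none to reproduce. Its expected number of diagnosed cases, in the Sample size section, is used below and was checked first.

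**Step 1. Confirmed cases expected by the plan.** 1.4 million x 6.2% = 86,800 (stated as approximately 86,600). With 63% undiagnosed, 86,600 x 0.37 = 32,042, as stated. As a share of the Electronic Staff Record population: 32,042 / 1,400,000 = 2.29%.

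**Step 2. Assumptions (not in the document).** App uptake is 10% in group A v 5% in group B, or 8% v 5%. In both groups 5% of users become app-positive, and a proportion g of all workers, 1% or 2%, has a suspected-case code. There is no true difference, and no person is counted by two routes.

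**Step 3. Suspected row.** Case proportion = g + uptake x 0.05. Expected IRR, B v A:

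| Uptake A v B | g | Calculation | IRR |
|---|---|---|---|
| 10% v 5% | 1% | 0.0125 / 0.0150 | 0.83 |
| 10% v 5% | 2% | 0.0225 / 0.0250 | 0.90 |
| 8% v 5% | 1% | 0.0125 / 0.0140 | 0.89 |
| 8% v 5% | 2% | 0.0225 / 0.0240 | 0.94 |

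**Step 4. Combined confirmed-and-suspected outcome.** Add 0.0229 to each proportion:

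| Uptake A v B | g | Calculation | IRR |
|---|---|---|---|
| 10% v 5% | 1% | 0.0354 / 0.0379 | 0.93 |
| 10% v 5% | 2% | 0.0454 / 0.0479 | 0.95 |
| 8% v 5% | 1% | 0.0354 / 0.0369 | 0.96 |
| 8% v 5% | 2% | 0.0454 / 0.0469 | 0.97 |

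**Step 5. Direction.** If group B has the higher uptake, the ratios invert: 1/0.94 to 1/0.83 = 1.07 to 1.20 for the suspected row, and 1/0.97 to 1/0.93 = about 1.03 to 1.07 for the combined outcome. With equal uptake the ratio is 1.00.

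**Step 6. Size against the plan's precision.** The false absolute differences are (0.10 - 0.05) x 0.05 = 0.25 percentage points and (0.08 - 0.05) x 0.05 = 0.15 percentage points. The Sample size section claims precision of 0.1% (Asian v White) and 0.2% (Black v White) for infection. Both differences exceed the first figure; only the larger exceeds the second.

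**Step 7. A second model, suspected row only.** Let c be the chance that a true case has a primary care code, and u the uptake, with every app user who is a case reporting it. The chance of capture is 1 - (1 - c)(1 - u).

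- c = 10%, uptake 10% v 5%: 0.145 / 0.190 = 0.76.
- c = 37%, uptake 10% v 5%: 0.4015 / 0.433 = 0.93. For Asian v White in the Electronic Staff Record at 6.2% infection, the 95% interval is 0.90-0.96.
- c = 37%, uptake 15% v 12%: 0.4456 / 0.4645 = 0.96.

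This model omits swab-confirmed cases, so it says nothing about the combined outcome.

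**The case against.** The strongest reply is that the damage is contained. Primary care codes are a second route that does not depend on the app. Confirmed-only diagnosis is a parallel main outcome without app data, so readers can compare the two. App data are to be used only where available. The Discussion already presents suspected cases as a trade of specificity for capture. Overlap between app and swab cases would shrink the Step 4 figures further. All of this stands, and it limits the size of the problem. None of it removes the mismatch, because no planned analysis would show how much of a suspected-case ratio comes from uptake.

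A reader might also infer three stronger points that the document does not support:

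- **That swab-positive workers without an app entry or code are non-cases in the combined outcome.** The suspected row lists no swab source, but the combined outcome reads naturally as the union of the two Table 3 rows. The Discussion supports this by describing the use of both kinds of diagnosis to capture more infections.
- **That the bias understates risk in ethnic minority groups.** This requires lower uptake in those groups, and the document gives no uptake by group.
- **That the plan contradicts its own criticism of symptom trackers.** The Discussion says of another study "thus results are at risk of selection bias due to reliance on accurate self-reporting of exposures and outcomes", but that study relied on tracker data alone. This plan adds primary care codes and does not itself describe its app as voluntary. The passage shows only that the authors know the hazard.

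**Conclusion.** The concern holds for the suspected row and, diluted, for the combined confirmed-and-suspected outcome. Table 3 fixes the case definition, the sources and the model, and Outcome incidence fixes the denominator, so this is a stated choice and not a detail left for later.

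Under the Step 2 assumptions the artefact is about 6-17% on the suspected-row ratio and about 3-7% on the combined outcome. These figures rest on assumed uptake, app positivity and coding rates, no overlap, and the plan's own 2.3% diagnosed. They show what a modest uptake gap would do and do not predict the actual bias. There is bias only if uptake or reporting differs by ethnicity or occupation beyond the four core predictors. Confirmed-only diagnosis is untouched. The change is worth making because it protects the main exposure contrast at little cost.

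**What to change.** 1. In Table 3, define the full-cohort suspected component by suspected-case SNOMED CT codes, and state that the combined outcome is a positive swab or such a code.
2. Analyse app-derived cases separately, among HCWs with a linked app record, with person-time taken from app use (for example first to last log). With that denominator the uptake term cancels.
3. Report app linkage by ethnic and occupational group, so that readers can judge how far uptake differs.

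A lighter alternative is to keep the present definition and add a sensitivity analysis without app-derived cases, alongside item 3. That would show the artefact but leave it in the main estimate.

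The cost is a change of wording in Table 3, one extra analysis and one descriptive table. The full-cohort outcome will have fewer suspected events, and the app analysis will apply only to self-selected users.

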## Methods

### Study design

We will use data from multiple linked electronic health record (EHR) databases to investigate the study hypotheses within a cohort of HCWs. The cohort study will begin on 1 February 2020 (date following first confirmed COVID-19 case in UK) and follow participants for 1 year, until 31 January 2021.

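### Among confirmed cases, All hospitalisations and COVID-19 ITU admissions count admissions that ended before the first positive swab, and the three logistic rows give late-diagnosed cases incomplete follow-up

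*Protocol article*

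**What the plan says.** In the protocol article, Outcomes section, Table 3, the relevant entries are:

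- **All hospitalisations:** "Any hospital admission recorded during the study period". The listed subgroup is confirmed COVID-19 diagnosis, and the model is logistic regression giving an OR.
- **COVID-19 ITU admissions:** an ITU admission at any point in the study period, with the same subgroup and model.
- **COVID-19 hospitalisations:** an admission carrying a COVID-19 ICD-10 code, or a "positive swab test for SARS-CoV-2 recorded during or within 28 days prior to admission". Subgroup and model are again the same.
- **Confirmed diagnosis**, which sets entry to the subgroup: "A positive swab test for SARS-CoV-2 during the study period".

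The Study design section says the cohort will "follow participants for 1 year, until 31 January 2021". The Observation period section starts the broad cohort's clock on 1 February 2020 and stops it at death or 31 January 2021. It does not restart the clock at the swab.

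The Outcome incidence section says rates will be reported in the whole cohort and "within subgroups who have experienced preceding COVID-19 events". It adds that time from diagnosis to outcome will be summarised. The section on associations between ethnicity, occupation and outcomes refers back to Table 3 for the regression models.

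**The concern.** Subgroup entry and outcome share one calendar window, and for two rows nothing fixes their order. A worker admitted in March 2020 for an unrelated reason who first tests positive in December 2020 is an event in the confirmed-case analysis of All hospitalisations. The same would hold for an earlier, unrelated ITU stay.

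The window also closes for cases and outcomes on the same day. A worker diagnosed in late January 2021 and admitted in February enters the logistic model as not hospitalised. The mortality rows use a time-to-event model, which can censor; the three hospitalisation rows do not.

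Hospitalisation is a main outcome and ethnicity the main exposure. An OR computed within confirmed cases will naturally be read as a comparison of what follows infection. If part of the numerator is earlier general morbidity, the OR is diluted. It could also move in either direction if background admission differs between groups. Adjusting for age, sex, comorbidity count and deprivation does not restore the order of events or supply missing follow-up.

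**Working it through.** **1. The plan's own counts (Sample size section).** 1.4 million × 0.062 = 86 800, against 86 600 stated (0.2% apart). 86 600 × (1 − 0.63) = 32 042 diagnosed cases. 32 042 × 0.25 = 8010 hospitalisations, stated as 8000. The figures reproduce and are used below. None of them is in dispute.

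**2. Exposure to the fault.** From 1 February 2020 to 31 January 2021 is 366 days inclusive. A confirmed case can have from 0 to 365 days of pre-swab time counted as outcome time, with post-swab observation shrinking correspondingly from 365 days to 0.

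**3. Pre-infection admissions (All hospitalisations row).** The article gives neither the background admission rate r nor the spread of diagnosis dates, so both are assumed: r of 5–15% a year, and diagnoses either even over the year or with 60% in the last 62 days.

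- Share of cases with a pre-infection admission: q = average over diagnosis day t of 1 − exp(−r·t/365.25).
- Share of scored events due only to such an admission, with 25% truly admitted for COVID-19 and independence: 0.75q / (0.75q + 0.25).
- Observed OR when the true OR is 1.5 (risks 0.25 and 0.333) and q is the same in both groups: each risk p becomes 1 − (1 − p)(1 − q).

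| Diagnoses | r | q | Cases of 32 042 | Share of events | Observed OR |
|---|---|---|---|---|---|
| Even | 5% | 2.46% | 789 | 6.9% | 1.47 |
| Even | 10% | 4.85% | 1553 | 12.7% | 1.44 |
| Even | 15% | 7.15% | 2292 | 17.7% | 1.41 |
| 60% in last 62 days | 5% | 3.51% | 1125 | 9.5% | 1.45 |
| 60% in last 62 days | 10% | 6.88% | 2204 | 17.1% | 1.41 |
| 60% in last 62 days | 15% | 10.11% | 3238 | 23.3% | 1.38 |

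A simpler check at 8% a year, with diagnosis on average two-thirds through the year: 32 042 × 0.08 × 2/3 = 1709 cases. Of these, 1709 × 0.75 = 1282 have no COVID-19 admission as well. 1282 / (8010 + 1282) = 13.8%.

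These shares leave unrelated admissions after infection out of the denominator. Including them would lower the shares somewhat. No figure is offered for ITU, because the article gives nothing to base one on.

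**4. Truncation at 31 January 2021 (all three logistic rows).** Cases with fewer than 28 days left: 28/366 = 7.65%, or about 2450, if diagnoses are even; 0.60 × 28/62 = 27.1%, or about 8680, if late-weighted. Most of these are still classified correctly, because only admissions after the cut-off are lost. With an assumed exponential swab-to-admission lag of mean 5 to 10 days, the share lost is the average of exp(−days remaining / mean lag):

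- even diagnoses: 1.4% to 2.7% of admissions (109 to 219 of 8010);
- late-weighted: 4.8% to 9.7% (387 to 773 of 8010).

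**The case against.** The best defence is that order is already stated. The Outcome incidence section cites Table 3 and speaks of preceding COVID-19 events. Table 3 gives one base definition per outcome, used for the whole cohort and the subgroups alike, and a journal article may leave the subgroup index date and window to a fuller plan. This shows what was intended. However, that sentence concerns incidence rates and sets no start or length of window, while the regression section points back to Table 3. Table 3 applied as written gives the wrong event set, so this is more than an omitted detail.

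Other objections stand and limit the point:

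- A reader might infer that every hospitalisation outcome counts admissions before infection. It does not: the swab route of COVID-19 hospitalisations requires a test during the admission or up to 28 days before it, and the other route requires a COVID-19 code.
- A reader might infer that everyone testing positive after 3 January 2021 is scored as a non-event. Anyone admitted by 31 January is an event. A swab taken during an admission has no lag to lose. The 28 days is a rule for attributing an admission to a test, not a promised follow-up.
- Adding pre-infection and COVID-19 admissions as if no one had both overstates the contamination, because the outcome is per person.
- The article does not explicitly say that the all-cause row is meant to measure severity after infection. That is inferred from the subgroup and from the Outcome incidence wording.
- Nothing in the article shows that infection timing differs by ethnicity or occupation.

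**Conclusion.** The point holds for All hospitalisations and COVID-19 ITU admissions within confirmed cases: Table 3 admits events that precede the condition defining the subgroup, and it conflicts with the Outcome incidence section. For All hospitalisations the likely effect is material but not overwhelming, with an OR of 1.5 attenuated to somewhere between 1.47 and 1.38. That range rests on assumed background admission and diagnosis timing, on the plan's 25% hospitalisation rate, and on equal background admission in the groups compared.

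Truncation is a secondary matter. It touches all three logistic rows and is small unless diagnoses cluster near the end of the year. A reader might conclude that the ethnicity or occupation OR is shown to be biased by it. The document does not support that: such bias needs diagnosis timing to differ between groups, which is not reported.

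The whole-cohort analysis is not at fault, since everyone in the broad cohort shares the same index date. This should be fixed, but it is not a defect that must stop the work.

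**What to change.** Treat order and late diagnosis as two separate changes.

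1. **Order.** For the confirmed-case analyses of All hospitalisations and COVID-19 ITU admissions, count only admissions in progress at the first positive swab or starting on or after it. Reword Table 3 to agree with the Outcome incidence section.
2. **Late diagnoses.** For all three logistic rows, choose one of two options. Either restrict to cases with a stated minimum post-swab follow-up before 31 January 2021 and count outcomes within that window (28 days, the interval in the plan's own swab rule, is one example), or model time from swab with censoring at study end.

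Leave the whole-cohort definitions unchanged.

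The cost is a few lines in Table 3 and some derivation work. The restriction option loses late-diagnosed cases: about 2450 of 32 042 under even diagnoses with a 28-day window, and more if cases cluster late. A short fixed window also drops later admissions and ITU transfers, and would drop coded COVID-19 admissions that ended before a first positive swab. It would make All hospitalisations among confirmed cases nearly the same as the swab route of COVID-19 hospitalisations. The time-to-event option avoids the fixed window but reports an HR in place of the planned OR.

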	Mortality due to COVID-19	any death registration with COVID-19-specific ICD-10 codes^3^ recorded for the primary or secondary cause of death during the study period	ONS mortality, primary care and secondary care data	Confirmed COVID-19 diagnosis COVID-19 hospitalisations COVID-19 ITU admissions	Flexible parametric time-to-event regression (HR)

*PHE Pillar 3 (serology testing for antibodies) and Pillar 4 (blood and swab testing) data will be incorporated if obtained.

†Symptoms include loss of smell or taste, fatigue, persistent cough and loss of appetite.^34^

‡COVID-19-specific ICD-10 codes are U07.1: ‘COVID-19, virus identified’ and U07.2: ‘COVID-19, virus not identified’.

CHESS, COVID-19 Hospitalisation in England Surveillance System; ICD-10, International Classification of Diseases—10th revision; IRR, incidence rate ratio; ITU, Intensive Therapy Unit; NHS, National Health Service; ONS, Office for National Statistics ; PHE, Public Health England; SNOMED CT, Systematised Nomenclature of Medicine Clinical Terms.

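### Table 3 labels an outcome COVID-19 ITU admissions but defines it as any ITU admission, and the same set then serves as a subgroup for both mortality outcomes

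*Protocol article*

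**What the plan says.** The section Outcomes names the main outcomes and refers to Table 3 for their definitions. In the table, the row COVID-19 ITU admissions is defined in full as "Admissions to ITU during the study period". Its sources are "Secondary care, CHESS, and intensive care audit data", its listed subgroup is confirmed COVID-19 diagnosis, and it is analysed by logistic regression.

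The neighbouring rows are written differently:

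- *All hospitalisations* is openly all-cause: "Any hospital admission recorded during the study period".
- *COVID-19 hospitalisations* needs either "hospital admissions with COVID-19-specific ICD-10 codes" or a "positive swab test for SARS-CoV-2 recorded during or within 28 days prior to admission".
- *Mortality due to COVID-19* needs COVID-19 ICD-10 codes "recorded for the primary or secondary cause of death during the study period".

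The running text lists the hospital outcomes as "hospitalisation (all, COVID-19 specific, ITU admission", so the ITU item stands apart from the COVID-19-specific item and carries no qualifier of its own.

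COVID-19 ITU admissions also appears in the subgroup column for both mortality rows. The section Outcome incidence says that each outcome is reported as the "rate of cases in the final UK HCW cohort and within subgroups who have experienced preceding COVID-19 events".

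**The concern.** The label promises a COVID-19 outcome and the definition delivers an all-cause one. A programmer who builds the outcome from the definition cell will count post-operative, trauma and other unrelated ITU stays as COVID-19 events. One who works from the label will add a criterion of their own. The two would produce different outcomes from the same protocol.

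Two sets of results are exposed. In the whole-cohort logistic models for ITU admission, the odds ratios for ethnicity and occupation become a mixture of the COVID-19 association and whatever association holds for general ITU use. In the mortality models within the ITU subgroup, the population at risk includes people who never had COVID-19, so hazard ratios presented as outcomes after COVID-19 critical care would describe a mixed group. Ethnicity contrasts in severe COVID-19 are a central purpose of the study, so the definition matters beyond tidiness.

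**Working it through.** **Comparison of the rows.** The documents state no ITU count, rate or precision, so there is no ITU figure to reproduce. The check is whether anything supplies the missing criterion.

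| Table 3 row | COVID-19 criterion in the definition |
|---|---|
| All hospitalisations | None, and the label claims none |
| COVID-19 hospitalisations | ICD-10 code, or positive swab in the 28 days before admission or during the stay |
| COVID-19 ITU admissions | **None, although the label claims one** |
| All-cause mortality | None, and the label claims none |
| Mortality due to COVID-19 | ICD-10 code as a cause of death |

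Possible repairs elsewhere:

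1. *Footnotes to Table 3.* They deal with Pillars 3 and 4, the symptom list and the ICD-10 codes U07.1 and U07.2. None adds a criterion to the ITU row.
2. *Data sources.* CHESS is a COVID-19 surveillance source, but the row also draws on secondary care and intensive care audit data, which are not limited to COVID-19.
3. *Subgroup column.* Confirmed diagnosis is an additional population. By the table's title and the section Outcome incidence, the outcome is also assessed in the whole cohort.
4. *Outcome incidence.* It describes the subgroups as people with preceding COVID-19 events. That conflicts with an ITU subgroup built on the written definition and does not amend the definition.

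Nothing closes the gap.

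**Illustration of size.** Two inputs are assumptions that do not come from the documents: the share p of COVID-19 hospitalisations that reach ITU (5% to 20%), and the yearly rate r of unrelated ITU admission among staff (0.05% to 0.2%). From the section Sample size come N = 1,400,000 staff in ESR, H = 8000 COVID-19 hospitalisations (32,042 × 25% = 8,010, so the stated figure is reproduced) and a 10.0% Asian share of the workforce.

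- COVID-19 ITU admissions: C = H × p = 8000 × 0.05 to 8000 × 0.20 = 400 to 1600.
- Unrelated ITU admissions: U = N × r = 1,400,000 × 0.0005 to 1,400,000 × 0.002 = 700 to 2800.
- Unrelated share of counted events, U/(U + C): from 700/2300 = 30% to 2800/3200 = 88%.

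Suppose the true rate ratio for COVID-19 ITU admission is 2.0 in the 10% group and unrelated ITU use does not differ. The COVID-19 ITU rate in everyone else is b = C/[N × (0.9 + 2 × 0.1)] = C/(1.1N). The apparent ratio is (2b + r)/(b + r).

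- C = 1600, r = 0.0005: b = 0.00104, ratio = 0.00258/0.00154 = 1.68.
- C = 800, r = 0.001: b = 0.00052, ratio = 0.00204/0.00152 = 1.34.
- C = 400, r = 0.002: b = 0.00026, ratio = 0.00252/0.00226 = 1.11.

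The events are rare, so odds ratios behave almost identically.

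**The case against.** **The label shows the intent.** Together with the wording on preceding COVID-19 events, the label suggests that a restriction was meant and not written down. This is fair: the documents do not show that the authors chose to analyse trauma or surgical stays as COVID-19 events. But the other COVID-19 rows for hospitalisation and death spell out their criterion, and the running text separates ITU from the COVID-19-specific item, so intent is not settled. If all ITU stays were meant, the label and the mortality subgroup are wrong instead. The row needs correcting either way.

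**There is partial protection.** ITU admission is also analysed within confirmed cases, and COVID-19 mortality still requires a coded cause of death. Both points stand. A reader might infer that unrelated deaths are counted as COVID-19 deaths in the ITU subgroup. They are not; only the population at risk is mixed. Neither safeguard reaches the whole-cohort ITU analysis or the make-up of the subgroup.

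**Timing.** A reader might also infer that, among confirmed cases, admissions months before the positive test are meant to count as outcomes, or that *All hospitalisations* has the same fault. The documents do not support this. Outcome incidence speaks of preceding COVID-19 events and plans to summarise the time from diagnosis to outcome, and *All hospitalisations* is all-cause by design, as all-cause mortality is. What remains is that Table 3 does not repeat the ordering.

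**The numbers.** The ITU rates are not in the documents, the protocol calls 8000 a minimum, and the widest results pair opposite extremes. This objection stands in full, so the figures carry no weight in the conclusion.

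**Conclusion.** The concern holds as a contradiction between a label and its definition, carried into a subgroup. As written, the rule produces an outcome and a mortality subgroup that are not what they are named. It is not a detail left to a fuller plan, because the article does state a definition and that definition conflicts with its own label.

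The ITU odds ratios move towards those of general ITU use. That is dilution towards 1 only if ethnicity and occupation are unrelated to other ITU admission, which the documents do not address. The size cannot be derived from the documents. The apparent ratios of 1.1 to 1.7 for a true 2.0 rest on assumed ITU rates and an assumed background ratio of 1. One of the seven Table 3 outcomes is affected, together with one of the three subgroups for each mortality outcome.

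**What to change.** 1. Redefine the row: a COVID-19 ITU admission is an ITU admission within a hospital spell that meets the plan's existing COVID-19 hospitalisation definition (U07.1 or U07.2, or a positive swab during the stay or in the 28 days before admission).
2. Add the Pillar 1 and Pillar 2 testing data to that row's sources, which do not list them at present.
3. Use this definition for both the outcome and the mortality subgroup.
4. If an all-cause ITU outcome was intended, rename that row to say so and keep the COVID-19 definition for the subgroup.
5. As a minor point, write the ordering from Outcome incidence into Table 3 for the confirmed-diagnosis subgroup, in a form that still admits a positive swab taken during the stay, as the COVID-19 hospitalisation row does.

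The cost is a few cells of Table 3 and the matching code. The testing data are already listed as sources for other rows. The protocol warns that not every outcome data set may be obtainable in every country, so the swab part may be unavailable in some. The COVID-19 hospitalisation row already carries that limitation, and it can be reported in the same way.
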